### Design of concurrent prospective observational sub-study

Detailed patient-level outcomes will be measured by systematic sampling across participating wards throughout the pilot trial as part of a prospective observational sub-study. One patient per ward per month will be recruited from all six included wards (*n* = 84) and we will collect data through a combination of self-report and continuous monitoring, the details of which are described under the ‘outcome measures’ section of this protocol. Written consent will be secured prior to participant recruitment. Patient eligibility will be established by the study research officer (RO) in consultation with the ward nurse manager or shift coordinator at each recruitment point. The RO will be responsible for securing participant consent. Some inclusion/exclusion criteria will apply to recruitment. We will exclude patients who have been admitted for longer than 30 days or are due to be discharged within the following 3 days. Patients that have been recruited to the current study in a previous month will also be ineligible for recruitment. Patients with known cognitive impairment will be excluded, as an important element of this sub-study is to capture data on participant subjective experiences and this would be infeasible among cognitively impaired patients. Due to lack of multi-language versions of the scales used in this study, we will also exclude patients who are not fluent in English. We will exclude patients who are unstable or deemed too unwell to participate. Finally, patients aged less than 65 years on the day of recruitment will also be considered ineligible for recruitment.

Prior to the start of the study, the principal investigator (PI) will produce 84 sets of computer-generated random integer sequences ranging from ‘1’ to the maximum number of bed locations in any ward, for example, ‘35’. These will then be printed and placed in sealed opaque unmarked envelopes and handed over to a RBWH Safety and Quality Unit (SQU) staff member who is not involved with the study. At each recruitment point, the RO will identify, in consultation with ward nursing managers, patients who are eligible to be approached for the study and a list of eligible bed numbers will be compiled and communicated to the nominated SQU staff member. The staff member will then open one envelope and will generate the order of recruitment as per the number sequence in the envelope. This list will be provided to the RO for commencement of recruitment. The PI will monitor recruitment to ensure adherence to the recruitment protocol. The RO will approach the first bed number on the recruitment order; if a patient does not consent to participate in the study, this process will continue until a patient is successfully recruited. This process will be replicated for each ward at every recruitment point.

### Sample size

For the cluster RCT, we are constrained by the available funding as to the number of wards that can be included in the pilot trial (six) and period for which data can be collected (14 months), and hence, the overall anticipated sample is estimated to be approximately 7500 patients. While it is more usual for pilot studies to be conducted with smaller sample sizes, physical design change of this nature has never been undertaken within a stepped wedge cluster RCT. Due to the potential of a variety of operational and logistical challenges in installing new equipment over entire wards, we anticipate that the feasibility of such an approach will only be confirmed by undertaking a rolling sequence of ward installations. In this regard, installations in six wards would provide sufficient opportunities to elicit the full range of practical challenges that may be experienced and afford adequate time to test and modify our implementation approach. Hence, the larger sample size of the study can be considered a secondary feature of this pilot study rather than a primary goal. Within these sample estimates, it is possible to directly calculate the likely effect size that we can detect with 80 % power. Power for parallel cluster randomised trial designs can be calculated by using a conventional power analysis approach and then applying a multiplier to compensate for a design effect, taking the formula [1 + (*n* − 1)**p*], where ‘*n*’ = the number of subjects per cluster and ‘*p*’ = the intra-cluster correlation coefficient to take into account the dependency of observations within clusters [63]. However, the stepped wedge design additionally has a ‘within-cluster’ element (that is, all clusters provide intervention and control data), which provides power advantages to a parallel cluster RCT in a similar way to the comparison of paired with unpaired *t* tests. Hence, a power calculation specific to stepped wedge designs is required. One previously described approach highlights that stepped wedge designs could reduce the required sample size in cluster randomized trials [64], but is based upon the cohort style of stepped wedge design where individual participants are repeatedly measured across the length of the study. This is not consistent with our planned study, which reflects more a cross-sectional style of stepped wedge where individual participants are likely to only have one measurement for their involvement in the study. Fortunately, another power analysis approach based on the cross-sectional style of stepped wedge trial better suited for examining a dichotomous outcome (that is, for comparing patients who fall with those who do not) has been developed [65]. Using this approach, our study has 83 % power to detect an absolute reduction in the proportion of patients who are fallers (patients who experience one or more falls) from 5 % (in control) to 4 % (in intervention) assuming 1071 patients per time period (total *n* ≈ 7500), a coefficient of variation of 0.4, and using six clusters (wards), seven time periods (six steps plus baseline) and a two-tailed alpha of 0.05. This represents a 20 % relative reduction in the proportion of patients who become fallers. We anticipate that the minimum important difference for our intervention is likely to be lower than this since an effect size as low as 5 % relative reduction could still represent a cost-effective solution. Nonetheless, in line with the pilot aims of this trial (primarily focused on feasibility), statistical power and cost-effectiveness are not primary considerations and will be the focus of a subsequent main study if the main aims of this pilot trial are satisfactorily met.

### Intervention

The lighting system specifications and installation scheme to be tested in the present pilot trial are aligned with prior research, described in detail by Figueiro and colleagues [46, 51, 58]. However, extensive in-hospital modelling and testing was undertaken by the investigative team in preparation for the present pilot trial guided by the United Kingdom Medical Research Council guidance on the development and evaluation of complex interventions [66]; certain design modifications were found to be necessary. These modifications were (a) incorporation of aluminium channels and diffusers (top plate) to house the LED luminaires in order to meet in-hospital durability and disinfection requirements, (b) elimination of the motion sensing feature described as part of an earlier trial in residential care settings [48], so as to avoid repeated and potentially disruptive cycles of activation and deactivation in multi-occupancy patient environments and (c) exclusion of under-bed lighting due to the risk of loss of lighting units when hospital beds are relocated, warranty concerns associated with affixing electrical devices to hospital equipment, and the possible confounding effects from the presence of integrated under-bed lighting in certain newer bed models procured at the RBWH. Proposed configurations and placement of remaining lighting elements for the present pilot trial will remain unchanged, although minor variations in installations are anticipated as electricians will need to accommodate for differences in design features and to negotiate any unexpected engineering challenges in individual rooms.

We will use commercially available LED strip lighting with an output wavelength of 670 nm (orange colour), which will be housed in aluminium tracks with diffuser cover strips. The lights will be installed in the following three locations across all patient rooms prior to each ward’s transition to the intervention phase:Around the exterior door frame of the attached toilet: To provide a visual reference point for patients attempting to mobilise to the toilet at night, we will install a continuous length of strip lighting around the exterior perimeter of the toilet door frame.Above the washbasin in attached toilets: In a horizontal section below the mirror and above the washbasin.Behind the toilet/adjacent to the toilet: To facilitate easy visualisation of the immediate area around the toilet, we will install one section of lighting behind to the toilet (above the cistern) and in a second section over the grab rail (where a wall-mounted grab rail is installed along the closest adjacent wall). Due to known inter-ward variability in location of toilets, type and location of grab rails within attached bathrooms, it might not be feasible to install grab rail lighting in all locations (such as when the toilet is located equidistant from adjacent walls or if bilateral fold-back grab rails are installed on the posterior wall on either side of the toilet). In such instances, we will make pragmatic decisions on implementation feasibility and variation, which will be comprehensively catalogued by the PI in a study journal. Installation locations are also illustrated in Fig. 3 and should be considered in conjunction with images presented in prior studies [47, 48, 50–52, 58] for approximations of spectral and illumination characteristics.

**Fig. 3 Fig3:**
[figure not shown]
Illustration of in-room locations of lighting intervention and configuration of luminaire installation

RBWH electricians will install the LED lighting units and installations will proceed in fully operational ward environments, without bed closures or patient relocations. The PI will coordinate installations with ward managers to ensure that minimal disruptions to normal work flow occur while ensuring that electricians have adequate access to the ward environment to install and test the lighting and control systems. Output levels of individual luminaires have not been specified in the registered protocol as data of this nature was not available prior to commencement. While it is planned that luminaire output will closely follow output levels specified in prior research [48, 51], further calibration will occur during the installation process in consultation with clinical staff and thereafter left unchanged for the duration of the pilot trial. Resultant luminance (emitted light) will be measured in situ after installations are complete and reported on alongside pilot trial results to assist with replication. Activation of the lighting units will be automated to ensure that they are operational overnight (planned operation from 5 PM through to 7 AM). This will help maximise service life and reduce power consumption. The activation and deactivation times have been selected to ensure availability of the lighting during dark periods and so that local seasonal variations of sunrise and sunset times are accounted for. Importantly, none of the existing lighting will be altered in any way, and staff and patients will have full use of existing lighting in patient rooms and toilets if the installed night lighting was considered inadequate or required supplementation; for example, if additional light is required for patients with severe visual impairment, or if a medical emergency occurs.

### Outcome measures

In this pilot cluster RCT, we will test the directionality of intervention effects on ward level ‘rate of falls’ (number of falls per 1000 admitted patient days) and the proportion of patients who have one or more falls as an inpatient. Fall outcome data will be compiled from multiple sources, namely, (a) incident reports completed on the Queensland Health (QH) clinical incident reporting system, (b) periodic contact with the ward nurse unit managers to identify any potentially unreported falls and (c) data routinely extracted by clinical coders from patient medical records after discharge. The PI will extract aggregated clinical incident reports on a monthly basis to update the project database, adding any unreported falls identified by the RO through ward contact. Additional falls coded from medical records, length of stay, ward bed occupancy and general demographic data for patients in study wards will be extracted from the clinical costing and case-mix system maintained by RBWH Health Information Services (HIS). These coded data will be extracted 3 months after the conclusion of the trial. To explore the effect of the intervention specifically on night-time falls, we will also include a secondary sub-analysis of the ‘rate of falls at night’ (falls occurring between the hours of 7 PM and 6 AM) using the same statistical approach described here. We note that the decision to include this secondary analysis is a protocol modification that occurred after trial registration but before data was ready for statistical analysis.

The observational sub-study will help us in understanding the manner in which the modified environment might influence patient level outcomes. Outcome measures will primarily aim to capture data on sleep quality, overnight activity levels, insomnia and daytime sleepiness. Table 1 describes the tools that will be utilised to collect this data.

**Table 1 Tab1:** Primary outcome measures for observational sub-study

Construct	Tool	Description	Frequency of data collection
Sleep quality and overnight activity levels	Philips Actiwatch 2—Wrist Actigraph	In order to collect objective data on participant sleep quality, sleep fragmentation, total sleep and overall activity levels, we will use wrist actigraphy. Actigraphs are wearable sensors that allow logging of movement data and have been extensive used in clinical research. Actigraphy data has been validated against gold-standard polysomnography methods and offers a reliable tool for measuring sleep outside of a sleep laboratory environment [71].	Days 0, 3, 7 and 12, consisting of one initial interview and a maximum of three follow-up interviews, unless patient is discharged or moved to another room prior to day 12. Days 3, 7 and 12 data collection will occur ±1 day to accommodate for weekends and public holidays.
		We will be using a Philips Actiwatch 2, which is a small, rugged, waterproof wrist worn data logger with long battery life and will provide us with a measure of rest-activity patterns and sleep. The Philips Actiwatch range has been applied in over 30 clinical trials to date including the study of sleep-wake patterns in older acute patients [72, 73].	
		Upon recruitment, the research officer will apply the Actiwatch on the participant’s non-dominant wrist and re-check application and wearing behaviour at every researcher-participant contact point thereafter.	
Daytime sleepiness	Karolinska Sleepiness Scale (KSS) [74]	The KSS is a short 9-item self-report questionnaire that is a measure of a situational sleepiness. The KSS is sensitive to daily changes in levels of sleepiness [75].	As above.
Insomnia	Insomnia Severity Index (ISI) [76]	Insomnia is an important manifestation of sleep disturbance and thus an important construct to measure. The ISI is a brief validated 7-item self-report measure of the individual’s subjective perception of insomnia (sleep onset, maintenance and early and unintended waking) as well as amount of concern generated due to those symptoms. The ISI has been utilised in prior studies on insomnia prevalence in older admitted populations [77].	As above.

A secondary focus will be participant self-reported premorbid sleep quality, vision, hearing, functional status, self-reported causes for disruption to sleep in hospital, participant light dosage levels and overall satisfaction with the room physical environment. Data on environmental lighting (within participant rooms) will be captured continuously using environmental sensors and data loggers. Secondary measures and environmental monitoring modalities are described in Table 2. All measures will be collected at the initial interview. Wrist actigraph and environmental sensors will also be applied at the time of the initial interview. Repeat measures (with the exception of premorbid sleep, current vision and hearing status) will be collected every 3 days (plus or minus 1 day) up to day 12 or discharge/transfer, whichever occurs earlier. The collection of these data will provide a detailed context for understanding potential mechanisms of effect for the intervention.

**Table 2 Tab2:** Pre-admission participant characteristics and secondary measures for observational sub-study

Construct	Tool	Description	Frequency of data collection
Pre-admission sleep	Epworth Sleepiness Scale	To explore whether any reported insomnia or sleep fragmentation is new or pre-existing, we will administer the Epworth Sleepiness Scale (ESS). The ESS is a widely used and valid 8-item self-administered instrument for measuring for excessive daytime sleepiness [78]. Excessive daytime sleepiness is associated with a range of disorders and has been associated with falls in certain older groups [79].	Initial interview only (day 0)
Vision impairment	Impact of Visual Impairment Scale	As participant visual status would influence the benefit derived from an environmental lighting solution we will ask participants to self-rate the functional impact of any visual impairment using the Impact of Visual Impairment Scale (IVIS). The IVIS is a widely cited and validated brief five-item instrument [80], which measures impact of vision impairment in terms of difficulties with simple tasks. Individual IVIS items are suited to older people in the inpatient setting and measure constructs relevant to study aims.	As above.
Hearing impairment	Hearing Handicap Inventory for the Elderly—Screening	The presence of hearing impairment is of secondary interest to contextualise data on causes of sleep disruption as patients with hearing impairment may be less affected by environmental noise than those patients with unimpaired hearing. We will measure the functional impact of hearing impairment among study participants by using the Hearing Handicap Inventory for the Elderly—Screening (HHIE-S). The HHIE-S is a short ten-item measure of the social, emotional and functional impacts of hearing impairment rather than a definitive measure of the degree of hearing impairment [81]. However, as a self-report measure, it has demonstrated excellent reliability and specificity in detecting the level of impact of hearing loss [82].	As above.
Self-reported causes for disruptions to sleep	Interview questions formulated by investigative team.	Sleep disruptions can occur due to multiple factors in addition to light levels. Therefore, we will ask patients to what degree their sleep was disrupted by specific causes (rated on a 7-point Likert-type scale ranging from ‘Never’ to ‘Constantly’).	Initial interview (day 0) and repeated on days 3, 7, and 12 Maximum of three follow-up interviews, unless patient is discharged or moved to another room prior to day 12. Follow-up data collection will occur ±1 day to accommodate for weekends and public holidays.
		The specific items are ‘Pain or Discomfort’, ‘Anxiety and Thoughts’, ‘Feeling unwell’, ‘People talking in your room’, ‘Alarms and sounds from medical devices’, ‘Sounds made by other patients’, ‘Bright lights being left on overnight’, ‘Bright lights being switch on while you sleep’, ‘Staff providing care to you’, ‘Staff providing care to others’ and ‘Volume of someone else’s television’.	
		The current 11 items represent a refinement over a previous version that was developed after a review of the hospital sleep literature and modified following with admitted patients in the prior (unpublished) modelling research conducted by [name] et al. to inform the present pilot RCT.	
Functional status	5-item Barthel Index	We will measure patient functional status using the 5-item Barthel Index [83] to capture any variations in functional status as this would influence the interpretation of mobility data collected through continuous direct monitoring. The Barthel Index is a widely used, valid and accepted tool for screening and assessing independence in activities of daily living (ADL) in geriatric settings, including older hospitalised patients.	As above.
Satisfaction with the room environment	Multiple choice question and free-text	To evaluate overall participant satisfaction with the physical environment of the room and bathroom, we will ask participants to rate their level of satisfaction on a 5-point Likert-type scale ranging from ‘Very satisfied’ to ‘Very Dissatisfied’. We will ask participants to suggest potential improvements to the physical environment that could help patients to feel more confident to move about safely in their room and bathroom, to sleep better or to assist patients in any other way.	As above.
Participant light dosage	Philips Actiwatch 2—integrated light sensor	The inbuilt light sensor will enable measurement of dosage of ambient white light over a 24-h period. We will set the sampling rate to one measurement every 30 s.	Continuous measurement (commenced at initial interview and continued for period of follow-up
Overnight maximum lighting levels and variation in patient room and toilet.	HOBO U12-012 Light Data Logger	As the modified lighting will be installed both inside the patient room and attached toilet, we will monitor variations in overnight lighting levels using a data logger (Onsetcomp HOBO U12-012) mounted on the wall in the patient room and toilet. The HOBO U12-012 data logger is a high-frequency, high-resolution device capable of a measuring range between 1 and 3000 lumens/square foot. As the Actiwatch sensor will be the primary measure of participant white light dosage, we will affix the data logger outside the immediate patient bedside environment (outside the area circumscribed by patient privacy curtains) in order to measure overall variation in room lighting profile. We will set the sampling rate to one measurement every 30 s.	As above.
Frequency with which toilet doors are opened and closed overnight	Onsetcomp HOBO UX90-001—State Change Data logger	In order to understand whether participants may have been exposed to the modified lighting environment within the toilet overnight, we will log the times of door opening and closing. This will be done through an unobtrusive door mounted data logger that measures contact with a magnetic latch (Onsetcomp HOBO UX90-001). Thus, all state change events (door opening and closing) will be captured. The HOBO UX90-001 is a high-capacity data logger appropriate to measuring simple state changes and will allow us to contextualise activity levels at night.	As above.

A final issue relates to the measurement of intervention fidelity. While intervention delivery itself does not require monitoring in this trial due to the automated nature of the intervention, it will be important to understand whether patient and staff usage of existing lighting is different before and after installation. Undertaking night-time visual observations was not considered possible within the limited scope of this pilot trial. We therefore sought to collect data on lighting usage through the implementation of automated environmental monitoring solutions. ‘Illuminance’ data (incident light on a given surface expressed in ‘Lux’ or lumens per square metre) will be collected in both pre-implementation and post-implementation phases through the use of sensors (with data logging capabilities) affixed in rooms and toilets of patients recruited to the observational sub-study. Through comparison of these data with visually validated reference data collected in the study wards, we will be able to classify the majority of room lighting states with a high degree of confidence (that is into ‘non-lit’, ‘LED lighting only’ and ‘operational ceiling lights’ categories). Further, we will be able to identify the timing, frequency and duration of intervals between state changes. While it would be difficult to attribute state changes to patients or staff based upon  this data alone—comparison with patient time-stamped sleep and activity data collected via wrist actigraphs will help us exclude patient action in some instances where the recruited patient was clearly not the agent causing the state change (for example, if actigraphy data indicates the patient was asleep).

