
We hypothesised that the introduction of a LED-based night lighting scheme (the ‘intervention’) in hospital rooms may contribute to fewer falls through several mechanisms (Fig. 1), but primarily through safer overnight ambulation among patients and reduced sleep disruption. We also hypothesised that the intervention would reduce peak lighting levels at night without impeding overnight usage of toilets by patients and would enhance the perceived environment from a patient perspective.

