### Statistical analysis

The analysis of primary outcomes will be with multi-level mixed effects generalised linear models using a Bernoulli family and logit link for the ‘proportion of patients who become fallers’ outcome and a negative binomial family and log link for the ‘rate of falls’ outcome. In these analyses, patient admissions will be nested within ward in the random effects part of the equation to take account of clustering of data by ward. The fixed part of the equation will examine group effects (intervention vs control phases) and adjust for time period. We will also adjust for seasonal effects on fall rates (that is, we will enter a covariate based on how many falls there were on each ward over the same time period over the previous 2 years). In relation to the observational sub-study, we will employ a full range of descriptive statistics to model the main features and distribution characteristics of the final data set. We will explore differences in patient sleep data and self-reported sleep and mobility behaviour collected over control and intervention periods through both qualitative and quantitative methods. Longitudinal data collected through actigraphy and environmental sensing will be subjected to exploratory analysis using pattern recognition and data filtering algorithms to classify the raw outputs against specific activity and event markers. Aggregated environmental sensing data will be graphically modelled through the development of scatter plots and histograms for visual identification of patterns and differences between control and intervention data. Categorical data on the causes of sleep disruptions collected through the patient interview tool will additionally be subjected to content [67] and thematic [68] analysis. Concurrently, we will undertake multi-level mixed effect generalised linear modelling with the quantitative data from the observational sub-study, using a Gaussian family and identity link for normally distributed continuous data. The random effects would be subjected to nested analysis; however, the fixed effect cannot adjust for seasonal variation, as we will not have access to any prior data of this nature.

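### The only control-intervention comparison named for the light-logger data is visual reading of aggregated plots, which, if aggregated by phase, mixes the lighting effect with ward mix and calendar time

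*Protocol article*

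**What the plan says.** The fidelity paragraph of the Outcome measures section explains that the lighting is automated, so its delivery needs no monitoring, but that "it will be important to understand whether patient and staff usage of existing lighting is different before and after installation". Loggers in the rooms and toilets of sub-study patients are to be classified into lighting states, one of which is ceiling lights on, and "we will be able to identify the timing, frequency and duration of intervals between state changes". The Background adds a related hypothesis, that "the intervention would reduce peak lighting levels at night".

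The Statistical analysis section treats these data in three steps:
- Longitudinal sensor output is "subjected to exploratory analysis using pattern recognition and data filtering algorithms to classify the raw outputs".
- Plots come next: "Aggregated environmental sensing data will be graphically modelled through the development of scatter plots and histograms for visual identification of patterns and differences". The differences meant are those that separate the two trial phases.
- A model runs alongside the plots: "we will undertake multi-level mixed effect generalised linear modelling with the quantitative data from the observational sub-study". Only one family and link is named for this model, and it carries a condition: "using a Gaussian family and identity link for normally distributed continuous data".

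On time, the section says of the sub-study model that "the fixed effect cannot adjust for seasonal variation, as we will not have access to any prior data of this nature". For the fall outcomes, the same section does state an adjustment for time period.

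**The concern.** In a stepped wedge, a raw contrast of control data with intervention data is not a fair comparison. Wards that switch early contribute mostly intervention data, wards that switch late contribute mostly control data, and intervention data come later in the calendar. The analysis has to deal with ward and time, as the plan does for falls. A histogram per phase does neither, and reading it by eye gives no estimate or interval.

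Use of existing lights bears on the mechanism that the pilot wants to examine. The Discussion lists data to test the postulated mechanisms among the things that give the pilot its value. A difference produced by ward mix or season could be read as a change in light use, or could hide one, and the main trial would inherit that reading.

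**Working it through.** **Inputs from the protocol article.** Six wards, 14 months, one ward switching every 2 months from month 2 (Design of stepped wedge cluster RCT). One sub-study patient per ward per month, n = 84 (Design of concurrent prospective observational sub-study). The document gives no between-ward variation and no time trend for light use, so those values below are assumptions.

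**Sample size.** 6 × 14 × 1 = 84, which reproduces the stated figure. The Abstract gives two patients per ward per month. That would double the counts but leave the shares below unchanged.

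**Ward mix.** The k-th ward to switch (k = 1 to 6) has 2k control and 14 − 2k intervention months. Each phase totals 42.
- First ward: 2/42 = 5% of control and 12/42 = 29% of intervention. Last ward: 12/42 and 2/42.
- Difference in weight, intervention minus control: (14 − 4k)/42, that is 10, 6, 2, −2, −6, −10, each over 42.
- Root sum of squares: √(100 + 36 + 4 + 4 + 36 + 100)/42 = √280/42 = 0.398.
- With an assumed between-ward coefficient of variation (CV) of 0.2: 0.398 × 0.2 = 0.08. With 0.4: 0.398 × 0.4 = 0.16.

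With no lighting effect, ward mix alone therefore gives the phase contrast a standard deviation of 8 to 16% of the mean, or about ±16% to ±31% at 95%. The order of wards is randomised, so this is chance imbalance and has no fixed direction.

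**Calendar time.** Number the months 0 to 13.
- The control months of ward k sum to k(2k − 1). Over the six wards: 1 + 6 + 15 + 28 + 45 + 66 = 161, and 161/42 = 3.83.
- All ward-months sum to 6 × 91 = 546. The intervention mean is (546 − 161)/42 = 9.17.
- Difference: 9.17 − 3.83 = 5.3 months.

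This shift is the same whatever order is drawn, so any trend in light use enters the phase contrast systematically.

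**Illustration by simulation.** 2,000 runs per scenario, 84 overdispersed counts, assumed mean 6, dispersion 0.5 and ward standard deviation 0.3 on the log scale. The Gaussian model has ward and period terms, with wards as fixed effects standing in for the mixed model.

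| Assumed log trend per month | True ratio | Pooled: mean difference | Pooled: rejects | Gaussian, ward + period: mean difference | Gaussian: rejects |
|---|---|---|---|---|---|
| 0 | 1 | 0.0 | 9% | 0.0 | 5% |
| −0.03 | 1 | −1.0 | 16% | 0.0 | 4% |
| −0.06 | 1 | −2.1 | 38% | 0.0 | 4% |
| 0 | 0.7 | −1.9 | 47% | −1.9 | 19% |
| −0.03 | 0.7 | −2.7 | 70% | −1.9 | 18% |
| −0.06 | 0.7 | −3.6 | 88% | −1.9 | 16% |

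The pooled contrast follows the trend and the adjusted model does not. The last column shows the price: low power with 84 observations once ward and period are in the model.

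**The case against.** The strongest reply is that the plots do not stand alone. The mixed-model sentence covers the quantitative sub-study data, the loggers are listed as sub-study measures in Table 2, and nothing excludes them. This stands. A reader might infer that light use will be judged only by eye and can get no valid estimate, but the text does not support that.

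A reader might also infer that a Gaussian model is imposed on counts and skewed minutes. It is not: the family is limited to normally distributed continuous data, and the families for other measures are left unnamed, which an analysis plan not shown may settle. The simulation also shows that a Gaussian model with ward and period terms gave nearly unbiased differences and about 5% false positives on overdispersed counts. The choice of family is therefore the lesser issue.

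Three further replies are fair. Aggregated need not mean collapsed into two phase pools, so the ward-mix and calendar figures apply only if it does. The fidelity paragraph asks whether use is different, not whether it falls; the directional hypothesis concerns peak light levels. And the Discussion says that the pilot's primary value is not in statistical testing.

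What these replies leave is that the one comparison named for environmental data is visual, that no light-use measure is assigned to the model, and that no period term is stated for it. The lack of prior-year data explains why the seasonal covariate used for falls is unavailable. It does not rule out a period term, which can be estimated within the trial because control and intervention wards run side by side in the five middle periods.

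**Conclusion.** The point holds as a weakness in how a stated comparison is set up. It does not show that the analysis is invalid. The plan calls the before-and-after question on existing lighting important, yet the only control-intervention comparison tied by name to the sensor data takes no account of ward or calendar time as described. The layout figures (5% against 29% of ward-months, 5.3 months later) follow from the design, on the reading that data are aggregated by phase and each ward-month counts equally. The 8 to 16% standard deviation also rests on the assumed between-ward CV of 0.2 to 0.4, and the simulation on its own assumed mean, dispersion and trends. The measure is exploratory and the trial is a pilot, so the consequence is limited. The change is worth making because it uses data already planned and a model framework already named.

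**What to change.** In the Statistical analysis section:
- Define, per monitored room-night and for a fixed clock window, the number of ceiling-light activations and the minutes in the ceiling-lights-on state. The document already uses two night windows (5 PM to 7 AM for lamp operation, 7 PM to 6 AM for night falls); state which one applies.
- Compare phases in the mixed generalised linear model framework already planned, with a family suited to each measure. Examples are negative binomial with log link for counts, as already chosen for the fall rate, and a log-link model for minutes.
- Use recorded hours as offset, random intercepts for ward and for room or patient, and a fixed calendar-period term.
- Report the intervention-to-control ratio with its 95% confidence interval, labelled exploratory.
- Keep the scatter plots and histograms as description, drawn by ward and period.

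The cost is some wording and a little analysis work, with no new data, devices or staff. The downside is a wide interval from 84 patients in six wards, which should be said in advance.
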